### Missing data

#### The endpoints

Number of days with migraine headaches in the past 4 weeks,Number of days with acute migraine-specific medication in the past 4 weeks,Number of days with non-migraine headaches of moderate or severe intensity in the past 4 weeks,Number of migraine attacks in the past 4 weeks,Number of days without headaches in the past 4 weeks,Cumulative length in hours of migraine in the past 4 weeks, andCumulative length in hours of non-migraine headaches in the past 4 weeks

are based on counting the number of days, attacks, or hours, respectively, from the headache eDiary. The respective endpoints will be set to missing if patients made entries for less than 80% of the days, i.e., for less than 22 out of 28 days. If patients made entries for at least 80% but less than 100% of the days, the missing number of days, attacks, or hours will be imputed by the average of the valid entries.

The primary efficacy endpoint of this study is based on the number of days with migraine symptoms in the past 4 weeks at 12 weeks after intervention in IV or after randomization in CO (FU12). At FU12, missing values might occur for several reasons. Generally, we assume that patients in CO are likely to stop diary entries for no specific reason. Missing values in IV might occur in the following scenarios:Patients in IV might stop the intervention and corresponding diary entries early because of no effect. Their missing values should therefore be comparable to the values in CO, and this scenario hence assumes that values are missing not at random (MNAR).Patients in IV might stop the intervention and corresponding diary entries early for other reasons not related to the outcome. Alternatively, patients in IV might only stop diary entries but keep the same level of adherence. Thus, missing values should be comparable to the observed values in IV, and this scenario assumes that values are missing at random (MAR) or missing completely at random (MCAR).

For the primary endpoint analysis, we assume scenario 1. Missing values are multiply imputed via construction of a joint distribution of the patients’ observed and missing data. This uses the jump-to-reference method as a special pattern mixture model, for which the distribution from CO is set as in reference [43]. From the generated imputation samples, *β*_1_ will be estimated using the above model in every data set. The estimates are then combined using Rubin’s rule [44]. Further details will be specified in the statistical analysis plan (SAP).

No other imputations of missing data will be performed, and all other analyses will be based on complete cases.

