### Sensitivity analyses

Sensitivity analyses of the primary endpoint will include variations in the handling of missing data. While details will be specified in the SAP, these will include (a) multiple imputation under the MAR assumption as in scenario 2 [45]; (b) complete cases analysis without imputation under the MCAR assumption; (c) imputation by baseline observation carried forward based on the baseline assessment in the FA set as a conservative approach assuming that withdrawing patients will return to their baseline values of the original levels of symptoms. Furthermore, the primary endpoint will be evaluated in the ITT and PP population. Further sensitivity analyses include the analysis of the secondary endpoints in the ITT and PP populations.

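### The five Holm-tested secondary endpoints are analysed on complete cases, while the primary treats missing intervention-group values as control-like, with no reason given and no missing-data sensitivity analysis for the secondaries

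*Protocol article*

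**What the plan says.** The Missing data section of the protocol article sets out two reasons for missing values in IV. In scenario 1, "Patients in IV might stop the intervention and corresponding diary entries early because of no effect". Their unseen values are then expected to look like CO values, and the article calls this MNAR. In scenario 2, dropout has nothing to do with the outcome, or only diary entry stops, so that "missing values should be comparable to the observed values in IV" (MAR or MCAR). For CO it states: "Generally, we assume that patients in CO are likely to stop diary entries for no specific reason".

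The choice between the scenarios is made for one analysis: "For the primary endpoint analysis, we assume scenario 1", carried out by jump-to-reference multiple imputation with CO as the reference. The section closes with: "No other imputations of missing data will be performed, and all other analyses will be based on complete cases".

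The Sensitivity analyses section opens with: "Sensitivity analyses of the primary endpoint will include variations in the handling of missing data". One of these is a "complete cases analysis without imputation under the MCAR assumption". The secondary endpoints are only repeated in the ITT and PP populations.

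The Statistical analysis section controls a family-wise error of 0.05 over the primary and secondary endpoints. The primary is tested first and the adherence-restricted migraine-day endpoint second. The other five secondaries then follow with Bonferroni-Holm, and a rejection is to be read as a demonstrated difference.

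**The concern.** A patient in IV who stops and has no usable week-12 diary is given a control-like value in the primary analysis and is deleted from the Holm-tested analyses. By the article's own label, deletion relies on MCAR. The article does not say why one patient's missingness should be informative in one analysis and uninformative in the next.

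The inconsistency is plainest for two endpoints. Response (at least a 30% reduction) is a function of the week-12 diary migraine days, so the primary analysis already produces imputed values from which it could be computed. Acute-medication days come from the same diary and become missing under the same 22-of-28-day rule.

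Repeating the secondaries in the ITT and PP populations does not help. It changes who belongs to the population, but the complete-case rule still applies within it.

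What is at stake is the size of the benefit reported on endpoints that the plan treats as confirmatory and that, according to the Discussion, go to the regulator. No planned analysis would show whether those results survive the assumption made for the primary.

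**Working it through.** **Inputs** (Sample size section): mean reduction 2.13 days in IV and 1.14 days in CO; SD of change 3.19; dropout 20% per group; two-sided α 0.05; power 0.80. The article gives no effect sizes or SDs for the secondary endpoints, so the migraine-day figures serve as an illustration only.

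**Step 1: reproduce the plan's own figure.** The plan sets dropouts to zero change in both groups: 0.8 × 2.13 = 1.704 and 0.8 × 1.14 = 0.912, a difference of 0.792. With SD 3.19, the two-sample t-test needs 255.6 patients, rounded up to 256 per group. This matches the stated 256.

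**Step 2: complete cases.** If CO dropout is unrelated to outcome, as the article assumes, the CO completer mean is 1.14. The IV completer mean is 2.13. The expected difference is 2.13 − 1.14 = 0.99 days.

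**Step 3: scenario 1.** A fraction d of IV has the CO mean:

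(1 − d) × 2.13 + d × 1.14 − 1.14 = (1 − d) × 0.99

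At d = 0.20 this is 1.704 + 0.228 − 1.14 = 0.792 days. It equals the planning difference in Step 1 because setting all dropouts to zero also multiplies 0.99 by 0.8.

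**Step 4: ratio.** Complete cases divided by scenario 1 is 1/(1 − d).

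| IV dropout d | Complete cases | Scenario 1 | Excess |
|---|---|---|---|
| 10% (assumed) | 0.99 | 0.891 | 11% |
| 20% (plan) | 0.99 | 0.792 | 25% |
| 30% (assumed) | 0.99 | 0.693 | 43% |

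**Step 5: other endpoints.** The algebra uses no property of migraine days. For any endpoint with IV completer mean m1 and CO mean m0, scenario 1 gives (1 − d)(m1 − m0). The same holds for a difference in response proportions. Here d is the share of IV missing on that endpoint. These are unadjusted expectations and assume that dropouts do not differ from completers in baseline covariates.

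**Step 6: scenario 2.** If missing IV values resemble observed IV values, the true difference is 0.99 and complete cases recover it. Jump-to-reference would then give 0.792, which is 20% too small (0.792/0.99 = 0.80).

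**Step 7: no treatment effect.** If m1 = m0 and missing IV values are control-like, all values share one distribution. The complete-case difference has expectation zero, and the test keeps its level.

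**The case against.** The article does not reject MAR or MCAR. It lists scenario 2 as possible, limits scenario 1 in words to the primary, and keeps MAR imputation and complete cases as sensitivity analyses of the primary. Calling complete cases 25% too large takes the conservative answer as the truth; under scenario 2 it is jump-to-reference that errs. This stands, and the claim has to be conditional. It does not supply the missing reason for treating the endpoints differently.

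A reader might infer that the Holm tests have an inflated false-positive rate. The article's own scenario does not imply this (Step 7). Inflation needs dropout tied to each patient's own poor result. A simulation with 256 per arm and 20% dropout gave a type I error of about 0.065 to 0.45 for latent correlations of 0.1 to 0.5, but no such correlation appears in the document. The Holm tests are also reached only after two earlier tests succeed, the first of them analysed by jump-to-reference.

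A reader might also extend the point to all six secondaries. The first removes non-adhering IV patients by definition, so many scenario 1 dropouts would leave it whatever the imputation rule.

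Nor is it certain that HIT-6, MIDAS and EQ-5D-5L lose the same patients. They are answered separately every 4 weeks, and the 22-of-28-day rule concerns the diary. Their d may differ from 20%, in either direction.

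Finally, this is not a detail left to the SAP. The article defers details of the primary's imputation, but it fixes complete cases for the rest outright.

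**Conclusion.** The concern holds in a conditional form. The article treats missing week-12 IV data as control-like for its primary endpoint and deletes patients with missing data for five confirmatory secondaries, without a reason and without any sensitivity analysis that would show the consequence. If scenario 1 is true and the treatment has an effect, complete-case mean differences on these endpoints are inflated by 1/(1 − d): 25% at the planned 20% dropout, and 11% to 43% over an assumed range of 10% to 30%. The migraine-day figures illustrate this; magnitudes on the HIT-6, MIDAS, EQ-5D-5L and medication scales cannot be derived from the document. The case is firmest for response and acute-medication days, which share the primary's diary and missingness rule, and less certain for the three questionnaires. The primary analysis is unaffected, and a false-positive problem is not shown. The plan should be changed, but the point does not threaten the trial's main conclusion.

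**What to change.** Derive 30% response from the imputed week-12 migraine days that the primary analysis already generates. Apply the same jump-to-reference imputation to HIT-6, MIDAS, EQ-5D-5L and acute-medication days, and make complete cases and MAR imputation their sensitivity analyses. If the sponsor prefers to keep complete cases as the main secondary analysis, the minimum is to state why and to prespecify the reference-based analysis as a sensitivity analysis for all five endpoints. Either change should be fixed before outcome data are examined.

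No new data are needed, since the diary is daily and the questionnaires are collected every 4 weeks. The cost is wording, extra programming, and secondary estimates that will be less favourable, and conservative if scenario 2 is the true state.

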### Sensitivity analyses

Sensitivity analyses of the primary endpoint will include variations in the handling of missing data. While details will be specified in the SAP, these will include (a) multiple imputation under the MAR assumption as in scenario 2 [45]; (b) complete cases analysis without imputation under the MCAR assumption; (c) imputation by baseline observation carried forward based on the baseline assessment in the FA set as a conservative approach assuming that withdrawing patients will return to their baseline values of the original levels of symptoms. Furthermore, the primary endpoint will be evaluated in the ITT and PP population. Further sensitivity analyses include the analysis of the secondary endpoints in the ITT and PP populations.

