### Sample size

The sample size was calculated with the aim to show a difference in the change in the number of days with migraine symptoms in the past 4 weeks at follow-up 12 compared with baseline.

To estimate the possible effect in the control group, eight studies were identified in which migraine patients in a control group received standard care or were placed in a waiting group [24–31]. These control patients were all aware of being in a control group, which is comparable to the planned study situation. Mean changes in migraine days with corresponding standard deviations and sample sizes were extracted from these publications and meta-analyzed using a random effects model. This yielded a pooled estimate of the mean change of 1.14 days.

The sample size was then calculated based on the following assumptions:Patients in the control group will experience a reduction similar to the reduction observed in the control groups in the literature, which was a reduction by 1.14 days on average.Patients in the intervention group will experience a reduction of at least 50% on average, which is recommended to be the minimally relevant effect [21]. Assuming that, at baseline, they will report a mean of 4.26 days as in our pre-study (internal data), this reduction corresponds to a mean change by 2.13 days.The drop-out rate is conservatively estimated to be 20% in every group. Although for the analysis of the primary endpoint, missing values will be imputed by multiple imputation, we assume a reduction of 0 days in patients with missing data for a conservative estimation of the sample size.In the intervention group, the average change is therefore estimated to be (0 days) × 20% + (2.13 days) × 80% = 1.704 days. In the control group, the average effect is therefore estimated to be (0 days) × 20% + (1.14 days) × 80% = 0.912 days.Based on values in the pre-study, the standard deviation of the change is set to 3.19 days.Significance level and power are set to α=0.05 (two-sided) and 1-β=0.8.To detect this effect using a two-group *t*-test requires that 256 patients per group are randomized (nQuery 4.0) [32].

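### Two-arm baseline carried forward is called conservative, but at the planned dropout it expects the same effect as the primary analysis, and it is stricter only if IV loses more patients

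*Protocol article*

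**What the plan says.** The primary analysis (Missing data section) imputes missing week-12 values by jump-to-reference with CO as the reference, on the reasoning that IV patients who stop for lack of effect will look like CO patients. For the control arm the same section says: "Generally, we assume that patients in CO are likely to stop diary entries for no specific reason".

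The Sensitivity analyses section then lists three variations in missing-data handling: (a) multiple imputation under MAR, (b) complete cases under MCAR, and (c) "imputation by baseline observation carried forward based on the baseline assessment in the FA set as a conservative approach". The reason given for (c) is that withdrawing patients go back to their original symptom level. Nothing restricts it to one arm, and the label does not depend on which arm loses more patients.

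The Sample size section supplies the planning figures. For CO it takes the literature reduction, "which was a reduction by 1.14 days on average"; for IV, "this reduction corresponds to a mean change by 2.13 days". On dropout it says "The drop-out rate is conservatively estimated to be 20% in every group", and for those patients "we assume a reduction of 0 days in patients with missing data for a conservative estimation of the sample size".

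**The concern.** A sensitivity analysis called conservative is normally read as one that is harder on the experimental arm than the main analysis. Baseline carried forward does that only to the extent that it takes more from IV than from CO. Here CO patients are themselves expected to improve, and the protocol sees no outcome-related reason for their stopping. Setting CO dropouts to zero change therefore takes away an improvement that the protocol expects, which pulls the comparison towards IV.

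At stake is how agreement between (c) and the primary would be read. The Discussion says the data go to the regulator as confirmatory evidence, and it expects high discontinuation in studies of this kind. If (c) agrees with the primary, a reader will take it that the result survived a harsher assumption about dropouts. At the planned dropout, no harsher assumption has been tested.

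**Working it through.** **Inputs (Sample size section).** Mean reduction among patients with data: 2.13 days in IV, 1.14 in CO. Dropout: 20% in each arm. SD: "the standard deviation of the change is set to 3.19 days". Test: "Significance level and power are set to α=0.05 (two-sided) and 1-β=0.8". Effects below are IV reduction minus CO reduction in days, so positive favours IV.

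**Reproducing the plan's figure.** 0.8 × 2.13 − 0.8 × 1.14 = 1.704 − 0.912 = 0.792. With SD 3.19, the normal approximation gives 255 per group and the exact t-test gives 256 (power 80.06%). The stated 256 is reproduced.

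**Expected effect under each analysis**, with dropout dI (IV) and dC (CO), dropout unrelated to outcome, and CO dropouts drawn from the CO distribution under jump-to-reference:

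- Primary: IV dropouts take the CO mean, so the effect is (1 − dI) × (2.13 − 1.14) = 0.99 × (1 − dI).
- (a) MAR and (b) complete case: 2.13 − 1.14 = 0.99.
- (c) Baseline carried forward: 2.13 × (1 − dI) − 1.14 × (1 − dC).
- (c) minus primary: 1.14 × (dC − dI).

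| IV dropout | CO dropout | Primary | (c) | (c) minus primary |
|---|---|---|---|---|
| 20% | 20% (planned) | 0.792 | 0.792 | 0 |
| 20% | 30% | 0.792 | 0.906 | +0.114 |
| 10% | 30% | 0.891 | 1.119 | +0.228 |
| 30% | 20% | 0.693 | 0.579 | −0.114 |
| 30% | 10% | 0.693 | 0.465 | −0.228 |

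Only the first row uses the plan's dropout figures. The others are an assumed range.

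**Against MAR and complete case.** (c) exceeds 0.99 only if 1.14 × dC > 2.13 × dI, that is dC/dI > 2.13/1.14 ≈ 1.87. With 20% lost in IV, CO would have to lose more than about 37%.

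**Precision.** Baseline carried forward enters a fixed zero for each dropout and treats it as observed, so it does not carry the uncertainty of imputation. In 1,500 simulated trials per scenario (256 per arm, baseline-adjusted linear model, 20 imputations combined by Rubin's rules, assumed baseline–change correlation 0.3), at 20%/20% both estimates averaged 0.788. The standard error was about 0.25 for (c) and 0.30 for the primary, and rejection was 87% and 79%. In the planned case (c) is the easier test to pass.

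**No true effect (both arms 1.14).** (c) then expects 1.14 × (dC − dI). At IV 10%/CO 30% that is 0.228 days in favour of IV, with simulated rejection of 14.9% for (c) and 2.6% for the primary. At IV 30%/CO 10% the same amount appears against IV.

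**The case against.** Several points on the other side are sound and limit the finding.

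- **(c) is stricter than its neighbours.** At planned dropout it gives 0.792 where MAR and complete case give 0.99, and it is stricter than the primary whenever IV loses more. A reader might infer that none of the listed analyses tests robustness to missing data. That goes too far: the primary is itself a reference-based MNAR analysis, and the list varies its assumption.
- **Higher CO dropout is not in the documents.** The plan assumes equal dropout. There are reasons to expect more loss in IV: it carries the glucose-sensor phase, food logging and weekly adherence questions, while CO only answers questionnaires and is offered the app after completion. A reader might infer that (c) will inflate the effect; the documents do not support that as a prediction.
- **The no-effect case rests on CO dropouts keeping their improvement.** Item (c) assumes the opposite, and the Discussion allows that trial participation and regular symptom logging may themselves reduce symptoms. If dropouts really return to baseline, (c) is not biased. A sensitivity analysis may test a different assumption, but that does not make it conservative relative to the primary.
- **The list is open.** It defers details to the SAP, so the absence of a tipping-point analysis from the article is no defect in itself. The label, however, is stated here.

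A reader might also extend the criticism to the zero-change step in the sample size. That does not follow. Planning on 0.99 days with SD 3.19 needs 164 evaluable patients per arm, or 164/0.8 = 205 randomized; the zero-change step gives 256. It is cautious there, and 0.792 matches the expected effect under the primary estimator.

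**Conclusion.** The point holds in a limited form. Two-arm baseline carried forward is not conservative in general, and not relative to the primary analysis. The planned-dropout result needs no assumption about unequal dropout: both analyses expect 0.792 days and (c) has the smaller standard error, so none of the three listed missing-data analyses is expected to be harder on IV than the primary. Away from equal dropout, (c) moves by 1.14 days times the dropout difference, in whichever direction the imbalance runs.

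This rests on the plan's own means, on dropout unrelated to outcome, and on jump-to-reference drawing CO dropouts from the CO distribution. Week-4 and week-8 data used in the imputation could shift the equality slightly. The standard errors and rejection rates also depend on the simulation settings given above. The consequence is confined to how robustness is reported; the confirmatory test is not affected.

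**What to change.** Remove the word conservative from item (c), or limit it to the comparison with the MAR and complete-case analyses. The two-arm version can stay in the list under a neutral description.

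For the stress test, penalize IV dropouts only and keep CO dropouts under MAR, in one of two ways:

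- A delta-adjusted tipping-point analysis on the jump-to-reference model, making IV dropouts progressively worse than CO by δ days. The expected effect is 0.99 × (1 − dI) − δ × dI, which is 0.792 − 0.2δ at 20% IV dropout.
- Baseline carried forward for IV dropouts only. At 20% IV dropout this expects 0.8 × 2.13 − 1.14 = 0.564 days, the same as δ = 1.14, and is below the primary at any non-zero IV dropout.

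If the SAP already contains such an analysis, only the label needs correcting. The cost is a wording change and one more imputation run, and the robustness result may look weaker. The sample-size text, N = 256 and the primary analysis need no change.

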## Discussion

This paper describes the design and the methodology of a randomized controlled trial on the clinical effectiveness of the DTx sinCephalea as prophylaxis of migraine. To the best of our knowledge, this is the first systematic clinical trial with a fully digital program to enable patients with migraine to follow a personalized low-glycemic nutrition in order to reduce their number of migraine days and the migraine-induced impact on daily life.

The study is designed to fulfill the regulatory requirements of the newly established Digital Healthcare Act bringing DTx into standard medical care. The clinical data will be handed to the Federal Institute for Drugs and Medical Devices (BfArM) for a thorough assessment. Confirmatory clinical data showing the superiority of the application of the DTx over the non-application of the DTx is required so that the DTx can be prescribed and will be fully reimbursed by the German statutory health insurance system.

Designing a clinical study using a DTx includes some obstacles, which must be addressed. DTx usually facilitate complex interventions with more than just one active ingredient as it would be the case in pharmacological treatments. Frequently, DTx are designed to allow lifestyle modifications, tracking of several activities, parameters, and conditions as well as using several channels for disease-specific educations. Consequently, a blinded control app is often out of the possibilities. A blinded control would require that at least the patient does not recognize whether he or she uses the intervention or the control DTx. There is the concept of a “sham-DTx” as an equivalent to a placebo control [46]; however, it has to be acknowledged that complex DTx with multiple possible ingredients potentially responsible for a clinical effect cannot be controlled well with a reductive version of the DTx [47, 48]. Consequently, the current gold standard for DTx studies is designing the control group as a wait-list control into which the patients are randomized [49–52]. This control group design is open-label by design and brings the obstacle of a missing blinding. Subsequently, it is possible that effect estimates will be biased by a “placebo effect”. This “placebo effect” might act on two levels: First, patients might be affected by the participation in the trial itself and the regular logging of symptoms, thus experiencing a reduction of symptoms. This might apply to both patient groups and thus not systematically bias effect estimates. Second, patients in the intervention group might additionally be affected by the knowledge of being in the intervention group, which might lead to an inflation of the effect when comparing the intervention group with the control group. To explore the extent of bias, in our study the adherence of patients to the recommendations will be assessed, and exploratory analyses will correlate the extent of adherence with the effects on migraine. Finally, results from this study are only applicable to patients who are able and willing to use this DTx. Comparing the baseline characteristics at inclusion visit between patients who do and do not participate in the main study will help to estimate the extent of this bias.

Another interesting aspect of working with DTx in a clinical study is that the use of a DTx brings the opportunity to include a digital outcome assessment. Digitally assessing the relevant outcomes has huge advantages: Patients can be reminded using app notifications, time stamps give information about the real timepoint of answering questionnaires, and in real-time the answers can be examined for consistency [53]. On the other hand, it has to be assured that the control group not using the intervention DTx uses a comparable manner of outcome assessment excluding a potential bias. In the current study, all participants in the control group use a modification of the intervention DTx which only allows for digitally answering the questionnaires. After completion of the study, all participants in the control group are offered to use the DTx, as part of a compensation of their effort.

A third obstacle by design is that apps and digital applications are frequently merely tested, and users may lose interest. Consequently, studies with apps and DTx usually face high rates of discontinued use. As well some participants are lost to follow up or simply drop out [54]. To address this issue, we only randomize participants who regularly used the app during the pre-study, thus indicating a long-term interest in its application.

This study is the first RCT with a completely digital nutrition program as prophylaxis of migraine and will bring valuable clinical data allowing confirmatory prove of the effectiveness of the DTx sinCephalea.

